### Medication

The study is open about the psychopharmacological treatment, with no treatment restrictions. On the basis of the study’s sample size, we expect equal distribution of type (classical versus atypical antipsychotics), dose, rate of non-adherence to medication, and prescription of other psychopharmacological treatment (antidepressants, mood stabilizers, benzodiazepines) in both treatment groups. Since the type and medication dose are potential confounders, they will be controlled.

### Data management and analysis

All analyses will be based, as far as possible, on the intention-to-treat principle. Differences in the primary outcome (adherence to pharmacotherapy) will be analyzed with a two-tail test for proportions with the Miettinen exact test [61]. A multiple logistic regression will be carried out to control for the confounding variables [62] using adherence (yes/no) as the outcome to verify the impact of the FPP on controlling the impact of the confounding variables (sex, age, severity of the disorder, cluster).

Survival analyses will be performed using the Kaplan-Meier method, followed by the log-rank test to define the terminal events at both the start of non-adherence and the first relapse or readmission episode [63]. Intention-to-treat will be applied considering the primary and secondary outcomes [64]. Multiple imputations will be applied to integrate missing data [65].

As far as validation of the self-report (MARS) and the interview (BARS) measure of adherence with respect to the blood levels of the main prescribed drug is concerned, Spearman’s rho will be used to compare blood levels of the main drug with the self-report or the interview; partial correlation will be used to ascertain the links between blood levels of the main drug with the self-report or the interview by taking into account the other measures (the interview or the self-report, respectively).

All analyses will be done with Excel (Microsoft Excel 2013 running on Windows 8) (Chicago, IL 60606, USA) or the Statistical Package for Social Science (SPSS) version 17 for Windows.

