**Methods:**

340 patients diagnosed with schizophrenia and related disorders according to standardized criteria from 10 participating units distributed throughout the Italian National Health System (NHS), will be enrolled with 1:1 allocation by the method of blocks of randomized permutations. Patients will be reassessed at 6, 12 and 18 months after start of treatment (duration: 6 months).

The primary objective is to evaluate changes in adherence to pharmacotherapy after psychoeducation. Adherence will be assessed at three-month intervals by measuring blood levels of the primary prescribed drug using high pressure liquid chromatography, and via the Medication Adherence Questionnaire and a modified version of the Adherence Interview. Secondary objectives are changes in the frequency of relapse and readmission, as the main indicator of the course of the disorder.

Enrolled patients will be allocated to the FPP (yes/no) randomly, 1:1, in a procedure controlled by the coordinating unit; codes will be masked until the conclusion of the protocol (or the occurrence of a severe negative event). The raters will be blind to treatment allocation and will be tested for blinding after treatment completion. Intention-to-treat will be applied in considering the primary and secondary outcomes. Multiple imputations will be applied to integrate the missing data. The study started recruitment in February 2013; the total duration of the study is 27 months.

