### Eligibility criteria

#### Inclusion criteria

Patients will be enrolled when they have a diagnosis of psychosis in the spectrum of schizophrenia according to the International Classification of Diseases - tenth edition (ICD-10: codes F20 to F29) and have been in contact with the unit for at least 24 months; admitting ages vary from 18 to 55 years old. Enrolled patients will be randomly allocated to FPP treatment (yes/no) with a rate 1:1, via a procedure controlled by the coordinating unit; codes will be masked until the conclusion of the protocol (or the occurrence of a severe negative event). Randomization will be carried out by the method of blocks of randomized permutations (to preserve balancing between the exposed and the non-exposed groups). Randomization will be stratified by location, due to the study’s multisite nature.

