### Randomization procedures and bias-minimization methods

All patients will be randomized in the exposed (FPP) or the unexposed (GT) group with a 1:1 allocation ratio in each unit, as each unit is expected to participate in the enrollment of both groups. Randomization will be carried out by the method of blocks of randomized permutations (to preserve balancing between the exposed and the non-exposed groups). Randomization will be stratified by location due to the multisite nature of the study. Correctness of the randomization procedure will be monitored at regular intervals.

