### Follow-up assessment

The FPP has a six-month duration, so patients will be assessed at entry (t0), at the end of the FPP (t1), at the six-month follow-up (t2), and at the twelve-month follow-up (t3), for secondary outcome measures. Adherence will be monitored at t0, t1, t2, and t3, via self-reports, interviews and measured blood levels of the primary prescribed drug.

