### Sample size and power

Sample size for the identification of the expected difference in the primary outcome (adherence to pharmacotherapy) was based on known evidence: prevalence of non-adherence to pharmacotherapy in patients already in contact with a psychiatric service is around 40 to 50%, median = 47% [11,12]; effect size of psychosocial treatment on various outcomes, including relapse, readmission and adherence to pharmacotherapy is 0.48 of the standard deviation (SD), with 95% CI= 0.10 to 0.85 [16]. We expect that our intervention could produce a change in the prevalence of non-adherence to pharmacotherapy in the exposed group with an effect size of 0.45 SD [11,12]. After performing a test of difference between proportions we determined that a sample of 78 participants per group would be needed to achieve 80% power to detect a difference with h = 0.45 (medium effect size) in the measures of adherence to pharmacotherapy, at a two-sided significance level of 0.05 and allocation ratio of 1:1.

Cohen’s h effect size for the difference of proportions is calculated on the formula:

$$h=2^{*}\arcsin\;p1-2^{*}\arcsin\;p2$$

where p1 and p2 are the proportions of adherent patients in the exposed group 1 and the non-exposed group 2, respectively [59]. The Cohen’s h measures the same effect size interval as the Cohen’s d but is based on differences by proportion rather than by continuous variables [59].

Cohen’s h = 0.45 implies that at the estimated power (= 80%) we can observe a 25.5% rate of non-adherence to pharmacotherapy in the exposed group as opposed to a 47% rate in the unexposed group. In this case, risk reduction is 0.215, corresponding to a number needed to treat (NNT) = 5. Since we do not know the exact proportion of non-adherence, here are the different starting p1 and related maximum p2 detectable:

p1: 0.65 0.60 0.55 0.50 0.45 0.40 0.35 0.30 0.25

p2: 0.43 0.38 0.33 0.28 0.24 0.20 0.16 0.12 0.09

Since this a multisite study, the clusterized nature of the data has to be controlled since it has an impact on an unequal variance by center, which requires a correction of the sample according to the formula:

$$\mathrm{DE}=1+\left(m-1\right)\times r$$

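### The named primary test is unadjusted: it uses neither the randomisation stratum nor baseline adherence, which costs precision but not validity

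*Protocol article*

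**What the plan says.** **Primary test.** Under Data management and analysis: "Differences in the primary outcome (adherence to pharmacotherapy) will be analyzed with a two-tail test for proportions with the Miettinen exact test". No stratum, covariate or effect estimate is attached to it.

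**Supporting model.** The same section plans a multiple logistic regression on adherence (yes/no), "controlling the impact of the confounding variables (sex, age, severity of the disorder, cluster"). Adherence at t0 is not in that list.

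**Missing data.** The same section adds: "Multiple imputations will be applied to integrate missing data".

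**Design features that bear on this.**
- Randomization procedures and bias-minimization methods: "Randomization will be stratified by location due to the multisite nature of the study".
- Follow-up assessment: "Adherence will be monitored at t0, t1, t2, and t3, via self-reports, interviews and measured blood levels of the primary prescribed drug".
- The abstract: "The primary objective is to evaluate changes in adherence to pharmacotherapy after psychoeducation".
- Sample size and power multiplies the sample by a design effect of 1.75 because of site, taking it from 156 to 273.

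**The concern.** Three things the trial builds in or collects do not reach the primary test.

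1. Site is a randomisation stratum and the stated reason for a 1.75-fold larger sample, yet the primary test pools over sites.
2. The objective is worded as change in adherence, and t0 adherence is likely to be a strong predictor of later adherence. Neither the primary test nor the listed logistic covariates use it.
3. Multiple imputation produces several completed data sets. Rubin's rules combine an estimate and its variance from each, and an exact p-value supplies neither.

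At stake are power if the true effect is modest, the sensitivity of the observed difference to a chance imbalance at entry, and a clear definition of the headline result after imputation.

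**Working it through.** **Inputs from the protocol article.** Non-adherence 47% versus 25.5%, h = 0.45, 80% power, two-sided 0.05, 1:1, 78 per group, ICC 0.05, ten units, 340 enrolled (170 per arm), 20% drop-out (170 × 0.8 = 136 per arm).

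**Assumptions, not in the documents.** The correlation r between t0 and follow-up adherence (0.3 to 0.7 shown), and a smaller effect of 47% versus 33% as an illustration.

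**Step 1: the plan's own figures.**
- n = 2(1.960 + 0.842)² / 0.45² = 77.5, so 78 per group. This reproduces.
- h for 47% versus 25.5% = 0.452.
- Design effect = 1 + 15 × 0.05 = 1.75, and 156 × 1.75 = 273. This reproduces.
- 273 / 0.8 = 341, close to the 340 enrolled.
- Unadjusted power at 47% versus 25.5%: 96.2% with 136 per arm, 98.7% with 170 per arm, before any site variation.

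**Step 2: ignoring site.** With arms balanced within site, the pooled test's variance is too large by roughly 1/(1 − ICC). Its actual size is then about 2[1 − Φ(1.96/√0.95)] = 4.4%. A simulation (ten sites, 17 per arm per site, 40,000 runs; pooled z-test versus site-stratified Cochran–Mantel–Haenszel test) gives:

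| ICC | Type I error, pooled / stratified | Power, 47% vs 25.5%, pooled / stratified |
|---|---|---|
| 0.02 | 4.8% / 5.3% | 98.5% / 98.5% |
| 0.05 | 4.4% / 5.1% | 98.1% / 98.3% |
| 0.10 | 3.8% / 4.8% | 97.4% / 97.9% |

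For a smaller effect (odds ratio 0.55, about 47% versus 33%) at ICC 0.05, power is 73.8% pooled and 74.8% stratified.

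The article does not define its exact test. If it behaves like Fisher's (assumed), its size without site effects is 3.7% and its power 98.2% at 170 per arm, so it too errs towards conservatism.

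**Step 3: ignoring t0 adherence.** Simulation with 170 per arm, 47% non-adherent at entry, no site effects, 8,000 runs; unadjusted test versus a test stratified by t0 adherence:

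| Assumed r | 47% vs 25.5%, unadjusted / adjusted | 47% vs 33%, unadjusted / adjusted |
|---|---|---|
| 0.3 | 98.6% / 99.1% | 75% / 78% |
| 0.5 | 98.7% / 99.7% | 76% / 86% |
| 0.7 | 98.5% / 99.9% | 76% / 95% |

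A rough formula agrees. For 47% versus 33%, h = 0.287, and power = Φ(h√(170 / [2(1 − r²)]) − 1.96) gives 75% at r = 0, 79% at r = 0.3 and 86% at r = 0.5. The factor 1 − r² is the linear-model result and only approximate here.

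**Step 4: size of chance imbalance at entry.** The standard deviation of the between-arm difference in t0 non-adherence is √(2 × 0.47 × 0.53 / 170) = 5.4 points. A difference above 5 points in either direction has a probability of about 2[1 − Φ(5/5.41)] = 36%.

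**Step 5: imputation.** The two-by-two table behind the exact test also yields a risk difference p1 − p2 with standard error √(p1q1/n1 + p2q2/n2). Rubin's rules can pool that, as they can the logistic coefficient. The article names neither as the primary result.

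**The case against.** The strongest reply is that nothing here is invalid. An unadjusted comparison of randomised arms has a null distribution that already allows for chance baseline imbalance, and Medication says the authors rely on sample size to balance non-adherence. A reader might infer from Step 4 that the result would be biased, or from Step 2 that false positives would rise. Neither follows: imbalance is a matter of precision, and ignoring site makes the test slightly conservative. This part of the reply stands.

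A reader might also infer that the plan ignores site altogether. It does not, because the logistic model includes cluster. Assessment and outcome measures also foresees analyses of covariance on a continuous adherence index. Its covariates are not listed, so that analysis cannot be said to exclude t0 adherence. This stands too, but neither analysis is the named primary test.

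A third tempting reading is that the exact test and multiple imputation cannot be used together. That is too strong. A risk difference from the same table can be pooled, p-values can be combined approximately after a normal transformation, and pooling detail may sit in a fuller document. What remains is that this article ties no poolable estimate to the primary test.

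Finally, at the planned effect there is almost no power left to gain. That is right, and it limits the point to smaller true effects. Smaller effects are not far-fetched: the Discussion allows that GT may prove as effective as the FPP, and the effect-size interval cited under Sample size and power reaches down to 0.10.

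**Conclusion.** The point holds as a recommendation on efficiency and clarity. The named primary test leaves out the randomisation stratum and t0 adherence, and the listed logistic covariates leave out t0 adherence.

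- **Site:** negligible at ICC 0.05, with type I error about 4.4% and about 0.2 power points lost at the planned effect.
- **Baseline adherence:** little to gain at 47% versus 25.5%, where power is about 98%. At 47% versus 33% with 170 per arm, power rises from about 76% to 78–86% for r of 0.3–0.5.
- **Imputation:** a gap in what the article specifies, not an incompatibility.

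The gain from baseline adherence rests on an assumed correlation and an illustrative effect, neither given in the documents. The power figures take all 170 per arm as analysed and do not model site and baseline adherence jointly.

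**What to change.** Before unblinding, make the already planned logistic regression the primary analysis, with arm, site, t0 adherence, age, sex and t0 severity.

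Enter t0 adherence as the t0 MARS or BARS score. The dichotomic index is built over repeated evaluations, so it has no identical version from a single baseline visit.

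Pool the treatment effect over imputations by Rubin's rules. The pooled quantity would be the log odds ratio, or a marginal risk difference with 95% confidence interval if the listed software (Excel or SPSS 17) allows it. Keep the exact two-proportion test as a supportive analysis.

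This needs no extra patients, visits or measurements. The cost is a change of wording and a modest reliance on a model. The adjusted log odds ratio is also conditional on the covariates, so it is not the same quantity as the crude difference in proportions.

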#### Exclusion criteria

Exclusion criteria are mental retardation or any severe cognitive impairment; psychosis due to substance abuse or to a medical condition; affective psychosis; co-morbid substance dependence; patient does not understand Italian; pharmacotherapy with depot. Inability or unwillingness to provide informed consent are additional exclusion criteria (see Table 1 for details).

**Table 1 T1:** Eligibility criteria

Inclusion criteria	Diagnosis of psychosis in the spectrum of schizophrenia (ICD-10: F20 to F29)
	Contact with the unit for at least 24 months
	Admitting ages varying from 18 to 55 years
Exclusion criteria	Mental retardation, or any severe cognitive impairment
	Psychosis due to substance abuse or to a medical condition
	Co-morbid substance dependence
	Patient does not understand Italian
	Pharmacotherapy with depot
	Inability or unwillingness to provide informed consent

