### Assessment and outcome measures

Assessment is aimed at investigating the clinical and functional status of the patients and evaluating the main effects of treatment on the primary and secondary outcome measures (Table 3). The primary outcome is the patient’s adherence to pharmacotherapy, intended as the continuous use of the primary prescribed drug. Even if patients with psychosis are generally under poly-pharmacotherapy, only adherence to the most important drug (the one expected to produce the main therapeutic effect), as indicated by the enrolling unit, will be monitored during the study. Adherence will be checked by a triple method of assessment: patient’s self-report on the Medication Adherence Rating Scale (MARS), patient’s replies to the four-query interview of the Brief Adherence Rating Scale (BARS), and measurement of blood levels of the prescribed drug. Data will be analyzed using two indicators of adherence:

1. a dichotomic index, where non-adherence is the lack of adherence to the treatment in 30% or more of the monthly evaluation on the self-report or the interview (since replies on both measures might not coincide);

2. a continuous index based on the scale - self-report or interview - which could be the most reliable by comparison with the measurement of blood levels of the primary prescribed drug, to apply statistical analyses of covariance and verify the impact of confounding variables on the primary outcome.

**Table 3 T3:** Timing of assessments of endpoints for efficacy and safety

	**T0**	**T1**	**T2**	**T3**
Background information (age, sex, diagnosis, and so on)	X			
Clinical Global Impressions	X	X	X	X
Brief Psychiatric Rating Scale (BPRS)	X	X	X	X
Positive And Negative Syndrome Scale (PANSS)	X	X	X	X
Social Performance Scale	X	X	X	X
Health of the Nation Outcome Scales (HoNOS)	X	X	X	X
World Health Organization Quality Of Life (WHOQoL)	X	X	X	X
The Family Questionnaire	X	X	X	X
Medication Adherence Rating Scale	X	X	X	X
Brief Adherence Rating Scale	X	X	X	X
Dosage Record and Treatment Emergent Symptoms Scale (DOTES)	X	X	X	X
Sheenan-Suicidality Tracking Scale (S-STS)	X	X	X	X
Modified Overt Aggression Scale (MOAS) 1.0	X	X	X	X
Blood sample for assessing of the blood level of the prescribed drug	X	X	X	X
Assessment of blinding				X

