### Relapse

For the purpose of this study, relapse is defined as any score equal to five or higher - for one month out of two or more - on the core symptoms of psychosis on the BPRS or PANSS, as defined above.

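### The survival analyses of start of non-adherence and first relapse do not fit patients who may already be in those states at entry, and the relapse definition requires no worsening

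*Protocol article*

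**What the plan says.** All places are in the protocol article.

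- **Data management and analysis.** Kaplan-Meier estimation is planned, "followed by the log-rank test to define the terminal events at both the start of non-adherence and the first relapse or readmission episode". The same section states: "Intention-to-treat will be applied considering the primary and secondary outcomes". Its opening sentence qualifies intention-to-treat as applying so far as it can. The primary analysis is a two-sided test of proportions, with a logistic regression of adherence (yes/no).
- **Inclusion criteria.** Patients have an ICD-10 F20 to F29 diagnosis and "have been in contact with the unit for at least 24 months; admitting ages vary from 18 to 55 years old".
- **Exclusion criteria.** The list includes "co-morbid substance dependence; patient does not understand Italian; pharmacotherapy with depot". Neither list mentions current adherence, remission or symptom level.
- **Sample size and power.** The "prevalence of non-adherence to pharmacotherapy in patients already in contact with a psychiatric service is around 40 to 50%, median = 47" per cent.
- **Assessment and outcome measures.** On the binary index, "non-adherence is the lack of adherence to the treatment in 30% or more of the monthly evaluation on the self-report or the interview".
- **Relapse.** For this study "relapse is defined as any score equal to five or higher - for one month out of two or more", applied to the core BPRS or PANSS items. The preceding section defines remission separately, and the relapse definition does not refer to it except to identify the core items.
- **Table 3 and Follow-up assessment.** BPRS and PANSS are rated at t0, t1, t2 and t3, which are entry, end of the six-month treatment, and six and twelve months later.

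**The concern.** A time-to-first-event analysis needs a population free of the event at the time origin and an event that marks a change of state. Neither is secured here. The enrolled patients resemble the service population in which the plan puts non-adherence near one half, and nothing at entry removes those already non-adherent or already symptomatic.

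Two things are at stake. First, the programme is meant to improve adherence, yet a first-onset analysis has no place for a non-adherent patient who becomes adherent. Second, relapse and readmission are named in the abstract as the main indicator of the course of the disorder. As worded, a relapse can be persistent illness with no deterioration, so the result could not be read as prevention of relapse.

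**Working it through.** **1. The plan's own sample-size figure.** n per group = 2 × ((1.960 + 0.842) / 0.45)² = 77.5, rounded up to 78, as stated. The rates 47% and 25.5% give h = 0.452. Then 156 × 1.75 = 273, and 273 / 0.80 = 341.25, close to the 340 enrolled. The sizing is for the primary binary comparison and is not in question. No survival analysis is sized.

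**2. Patients already non-adherent at t0.** Assumption: the literature rate in Sample size and power holds at entry.

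| Rate at t0 | Non-adherent, of 340 | Able to start non-adherence |
|---|---|---|
| 40% | 0.40 × 340 = 136 | 204 |
| 47% | 0.47 × 340 = 160 | 180 |
| 50% | 0.50 × 340 = 170 | 170 |

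At 47% about 90 patients per arm remain at risk (85 to 102 over the range).

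**3. How much of the planned effect lies among them.** Take 47% non-adherent at t0 in both arms, and at t1 47% under GT against 25.5% under FPP, a difference of 0.215. Link t0 and t1 by a latent bivariate normal variable. Its correlation is assumed; the document gives none. The table shows the probability of being non-adherent at both visits.

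| Correlation | GT | FPP | Difference | Share of 0.215 |
|---|---|---|---|---|
| 0 | 0.221 | 0.120 | 0.101 | 47% |
| 0.3 | 0.269 | 0.159 | 0.110 | 51% |
| 0.5 | 0.304 | 0.186 | 0.118 | 55% |
| 0.7 | 0.344 | 0.216 | 0.128 | 60% |

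Varying the t0 rate over 40 to 50%, with correlation 0.3 to 0.7, gives 44 to 64%. Roughly half of the hoped-for reduction is recovery, which an analysis of onset does not capture.

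**4. Why the unstated handling matters (illustration only).** Log-rank power was simulated for 340 patients, 47% non-adherent at t0, exponential onset, and visits at 6, 12 and 18 months. Incidence and hazard ratio are assumed.

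| 18-month GT incidence | Hazard ratio | Prevalent cases as events at time zero | Prevalent cases outside the risk set |
|---|---|---|---|
| 30% | 0.5 | 24% | 60% |
| 30% | 0.6 | 15% | 40% |
| 47% | 0.5 | 41% | 80% |
| 47% | 0.6 | 30% | 58% |

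The protocol commits to neither column.

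**5. Relapse, by reading the text.** A patient with one core item at 5 at every visit meets the threshold without any change, because no earlier score below 5 is required. The duration clause counts months, while the scheduled ratings are six months apart (0, 6, 12, 18), so the schedule cannot show whether it was met. The proportion at 5 or higher at t0 is not given, so no size can be put on this.

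**The case against.** The strongest reply is that the article is silent rather than wrong. It names no risk set and no time origin, and a condensed article may leave both to a fuller document. Speaking of a start and a first episode suggests incident events among patients at risk. That stands, and it rules out three stronger readings.

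- A reader might infer that about half the sample has its event at time zero. The document does not say so. Prevalent cases could be counted at t0, counted at t1 or left out. The 47% is also a literature median, used as the expected rate in the unexposed group, and not a stated t0 rate for this trial, which excludes depot users and applies its own index.
- A reader might infer that leaving prevalent cases out breaks intention-to-treat. The principle is stated with a qualifier, and a risk set defined by a baseline measurement does not clearly contradict it.
- A reader might infer that the relapse comparison is pulled towards no difference. This is not shown. If counting starts at t1, a patient who enters at 5 and improves avoids the event, so a treatment effect could register. The event also includes readmissions, which are recorded throughout.

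The reply also notes, correctly, that the primary test and logistic regression use adherence yes/no and so can register recovery. Randomisation balances prevalent cases in expectation.

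The silence does not excuse the relapse definition, which is written out in full, nor the choice of an onset analysis for an aim that is largely about recovery.

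**Conclusion.** The concern holds for the secondary survival analyses. If 40 to 50% are non-adherent at t0, 136 to 170 of 340 patients (160 at the median) cannot start non-adherence, and their recovery is not captured. The share of the planned reduction that falls among them is about 51 to 60% at the median rate, under an assumed correlation of 0.3 to 0.7. The handling of these patients is unstated, so the consequence is an undefined estimand and possible loss of power, not a demonstrated error in a result.

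The relapse definition, as worded, counts persistent symptoms as relapse and contains a duration clause that the visit schedule cannot verify. The number of patients affected and the direction of any bias are unknown. This should be corrected, but it does not threaten the primary comparison.

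**What to change.** 1. **Adherence.** Replace or supplement the survival analysis with a repeated binary model (GEE or mixed logistic) of adherence at t1, t2 and t3 in all randomised patients, adjusted for t0 adherence and site.
2. **Relapse.** Define it as a change from all core items below 5 to any at 5 or higher. Fix the risk set by t0 status only and analyse by visit interval. Patients at 5 or higher at t0 should not enter the risk set after improving, since that conditions on something treatment may influence. Add an all-randomised comparison of a score of 5 or higher at t1 to t3, adjusted for t0 status.
3. **Duration clause.** Reconcile it with the six-monthly ratings, either by stating how monthly status is obtained or by rewording it to what the visits can show.
4. **Readmission.** Keep Kaplan-Meier and log-rank, stratified by site, for dated readmissions.

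The cost is protocol or SAP wording. Adherence, BPRS and PANSS are already collected at t0, so no new data are needed unless item 3 is met by adding monthly information. The downside is fewer patients at risk in the incident-relapse analysis, which the all-randomised comparison partly offsets. The choice should be made before unblinding, so that the risk set is not picked after the results are seen.

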Psychoeducational programs were developed to improve adherence to pharmacotherapy by reducing irrational beliefs towards drugs and their side effects, increasing tolerance to the inevitable and unwanted effects, and promoting coping strategies and problem-solving skills to help face everyday problems associated with the disorder. Studies on the real effectiveness of these programs have found protective effects against the risk of relapse and on the probability of readmission, with medium effect-sizes: Cohen’s d = 0.18 (95% CI = 0.13 to 0.49) and d = 0.58 (95% CI = 0.27 to 0.89), respectively [16]. A 2011 meta-analysis including 5,142 participants from 44 independent trials conducted from 1998 to 2009 confirmed the effectiveness of psychoeducation in reducing relapse and readmission [18]. Participants receiving psychoeducation were also found to be more satisfied with mental health services and reported a better quality of life.

More complex intervention models involve both the patients and their families, because the disorder is chronic from its onset and can cause a heavy burden on the family: the patient is unlikely to preserve a reasonable level of autonomy and independence without the support of his/her relatives. For this reason, psychoeducation programs involving the family are more likely to produce positive results on the course of the disorder [16].

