A number of related, secondary outcomes will be assessed: the occurrence of psychotic symptoms, according to the Brief Psychiatric Rating Scale (BPRS) and the Positive and Negative Syndrome Scale (PANSS); the general level of psychopathology, according to the Health of the Nation Outcome Scales (HoNOS); changes in social functioning, according to the Personal and Social Performance scale (PSP), and in the quality of life, as evaluated on the WHO-Quality of Life-Short form (WHOQOL-Bref); changes in the patient’s overall clinical status, as measured by the Clinical Global Impression (CGI); changes in the dosage of the prescribed drugs, as a reflection of changes in adherence to therapy; and, finally, changes in the frequency of relapse and readmission. Italian validated versions of the scales will be used. The BARS and the Family Questionnaire (see below) were translated for this study.

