### Readmission rate

Readmission is defined as any admission to a psychiatric unit to treat symptoms of psychosis or to change the drug regimen. Admissions for somatic reasons will not be considered as episodes of readmission. All voluntary and involuntary admissions of participants at enrollment during the study and at follow-up will be recorded.

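### Relapse and readmission are set as a frequency objective, but the only analysis stated for them is time to a first event, most naturally read as one pooled event

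*Protocol article*

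**What the plan says.** All references are to the protocol article.

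- **Objective.** Abstract, Methods: "Secondary objectives are changes in the frequency of relapse and readmission, as the main indicator of the course of the disorder". Assessment and outcome measures closes its list of secondary outcomes with "changes in the frequency of relapse and readmission".
- **Definitions.** Under Relapse, "relapse is defined as any score equal to five or higher" on core BPRS or PANSS symptoms. Under Readmission rate, "Readmission is defined as any admission to a psychiatric unit to treat symptoms of psychosis or to change the drug regimen". One event comes from a symptom scale and the other from an admission record.
- **Data.** Readmission rate: "All voluntary and involuntary admissions of participants at enrollment during the study and at follow-up will be recorded".
- **Analysis.** Data management and analysis uses Kaplan-Meier and the log-rank test to "define the terminal events at both the start of non-adherence and the first relapse or readmission episode". The test for proportions in that section is for adherence, and the logistic regression is specified "using adherence (yes/no) as the outcome".
- **Cited effects.** Background gives d = 0.18 for relapse and, for readmission, "d = 0.58 (95% CI = 0.27 to 0.89), respectively".
- **Other wording.** Aims expects the programme to lower the risk of relapse and readmission, with effects maintained at both follow-ups.

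**The concern.** The objective asks how often patients relapse and are readmitted. The stated analysis asks how long it is until something first happens. These are different quantities. A programme that mainly prevents second and third admissions would show little in the stated analysis, even though every one of those admissions is recorded.

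The event itself is a second difficulty. The sentence announces two terminal events with the word *both*: the start of non-adherence, and a first relapse or readmission. Read that way, the second is a single combined event. An admission that follows a scored relapse then never counts, and the result cannot be attributed to either component. The Discussion part of the abstract would rest a health-service recommendation partly on reductions in relapse and in readmissions, so it matters which of the two moved.

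**Working it through.** **1. Objective against analysis.** The article states no power or sample-size figure for relapse or readmission, so there is none to reproduce for this outcome. (The primary calculation does reproduce: 2 × ((1.96 + 0.842)/0.45)² = 77.5, so 78 per group; 156 × 1.75 = 273; 273/0.8 = 341, against 340 enrolled. It has no bearing here.) Of the between-arm methods in Data management and analysis, the proportions test and the logistic regression concern adherence. Only the survival analysis names relapse or readmission. No stated method gives a count, a rate or a change in either.

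**2. Repeat admissions left out of the analysis.** Let P be the control risk of any admission over follow-up and m the mean number of admissions. The share that are repeats is 1 − P/m, with m = −ln(1 − P) for Poisson counts and m = ((1 − P)^(−k) − 1)/k for gamma-Poisson counts with dispersion k. The article gives no P or k, so P = 20% to 40% is assumed:

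| k | Repeat share |
|---|---|
| 0 (Poisson) | 10% to 22% |
| 1 | 20% to 40% |
| 2 | 29% to 55% |

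Example: P = 0.30, k = 1 gives m = (1/0.7 − 1)/1 = 0.429 and a share of 1 − 0.30/0.429 = 30%.

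Simulation with 136 per arm, an assumed rate ratio of 0.6, 0.4 to 1.0 admissions per control patient and k from 0.5 to 2 gives roughly 33% to 73% power for log-rank on first admission and 44% to 88% for a comparison of counts. The gain is about 6 to 25 points.

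**3. Effect of pooling, if that is meant.** Inputs:
- n = 340 × 0.8/2 = 136 per arm (enrolment from Overview, 20% drop-out from Potential limitations).
- Assumed control risks: readmission 30%, relapse 40%.
- Treated risk from odds × exp(−d·π/√3). Readmission d = 0.58: odds ratio 0.349, risk 13.0%. Relapse d = 0.18: odds ratio 0.721, risk 32.5%. Relapse d = 0.48, the pooled planning effect under Sample size and power: odds ratio 0.419, risk 21.8%.
- Pooled risk = relapse + readmission × (1 − overlap), where overlap is the share of readmitted patients already counted as relapsed.
- Power = Φ(|difference|/SE − 1.96), with SE = √(Σ p(1 − p)/136). Site effects are ignored. Using the pooled null variance moves results by about one point.

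Readmission alone: 0.300 − 0.130 = 0.170, SE 0.0488, power 94%.

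| Overlap | Pooled power, relapse d = 0.18 | Pooled power, relapse d = 0.48 |
|---|---|---|
| 30% | 90% | over 99% |
| 50% | 76% | over 99% |
| 80% | 45% (46.0% v 35.1%) | 97% (46.0% v 24.4%) |
| 100% | 25% | 91% |

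With readmission d at its lower limit of 0.27 and relapse d = 0.18, readmission alone has 42%, and the pooled event has 65% at 30% overlap and 52% at 50%.

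**4. Cross-check on the hazard scale.** All 340 patients, hazard ratio = ln(1 − p_treated)/ln(1 − p_control), Schoenfeld power, relapse d = 0.18, and the same control risks:
- Readmission alone: 0.39, power 98%.
- Pooled, independent components: (0.393 + 0.139)/(0.511 + 0.357) = 0.61, power 89%.
- Pooled, relapse always first: 0.77, power 31%.

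Over relapse risks of 30% to 60% and readmission risks of 20% to 40%, never above the relapse risk, the three ranges are 92% to 99%, 67% to 95% and 27% to 34%.

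**The case against.** Several points on the other side have force.

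- **Frequency and risk.** The article does not define frequency as a count, and Aims speaks of risk. Kaplan-Meier with log-rank answers a risk question. This stands: a reader might infer that the trial cannot answer its secondary objective at all, and that goes too far.
- **Pooling is one reading.** Because the two events are defined separately, the phrase could mean one curve for each. This stands as a possibility. It would remove the pooling issue, but repeat admissions would still play no part.
- **Hidden readmission effect.** A reader might infer that pooling must mask a benefit on readmission. The document does not support this. The relapse interval as printed (0.13 to 0.49) is not centred on 0.18 and overlaps the readmission interval. Background also reports relapse of 83% against 17% for this same programme, and with relapse d = 0.48 pooling loses nothing at 80% overlap. Complete overlap also fits the design poorly, since BPRS and PANSS are scheduled only at four visits while admissions are recorded throughout.
- **Omission in a condensed article.** The section names no between-arm analysis for the symptom or functioning scales either, so it is not exhaustive. That would answer a complaint about silence. Here an analysis is named for this outcome, and it does not match the objective.
- **Rank and data.** Only the abstract gives this objective prominence; the outcome list puts it last. No data are lost, because all admissions are recorded.

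**Conclusion.** The mismatch holds on the text alone. The objective is a change in frequency, the stated analysis is time to a first event, and on either reading of that phrase repeat admissions do not enter. If the events are pooled, the result cannot show whether relapse or readmission changed.

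The size is uncertain. Between about 10% and 55% of admissions would go unused, and a count comparison would gain about 6 to 25 points of power, all under assumed rates and dispersion. Pooling could take power from 94% to 45%, leave it at 97%, or raise it above that of readmission alone, depending on control risks, overlap and a relapse effect that the document does not fix. The case for change therefore rests on matching analysis to objective and on interpretability, not on a demonstrated loss of power. The matter is secondary and cheap to put right.

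**What to change.** In Data management and analysis:

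1. Name relapse and readmission as two separate secondary endpoints.
2. Compare the number of readmissions per patient over follow-up by negative binomial regression, with log observed time as offset and site as covariate.
3. Keep Kaplan-Meier and log-rank for first relapse and for first readmission, each on its own, as supportive analyses for the risk aim. Report any pooled first event descriptively only.
4. Adjust for prior admission count only if the units' records supply it over a fixed period. The entry criterion of 24 months' contact does not show that complete admission histories exist.

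The cost is a few sentences and one model on admissions already recorded. The downside is one more secondary test, so the two endpoints should be ordered or labelled in advance.
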